#### Participant safety

Individuals who show symptoms of heightened suicidality will be treated according to a standardized procedure, e.g., during the diagnostic telephone interview individuals will be excluded from study participation and strongly advised to seek help and support from their general practitioner or local psychiatric emergency room. All relevant information containing emergency contact numbers will be additionally sent via email. This procedure will also be followed should participants show symptoms of suicidality throughout the study phase. Additionally, participants already included in the study are contacted by an experienced clinician who will determine suicidality symptom severity and discuss next steps concerning their mental health.

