### Participants and procedure

#### Inclusion and exclusion criteria

We will include (1) adults (≥18 years), (2) with a diagnosis of MDD according to DSM-IV criteria assessed by diagnostic raters using the Mini international neuropsychiatric interview (MINI) (48), (3) internet access, (4) a valid email address, (5) sufficient skills in the German language in reading and writing, and (6) who agreed to the terms of this trial by providing signed informed consent. Individuals are informed that they can discontinue the study at any point without any consequences. Individuals will be excluded who (1) have a history of manic/hypomanic episodes, (2) or psychotic disorder, (3) are currently receiving psychotherapy for MDD or anxiety, (4) are on a wait-list for psychotherapeutic treatment, or (5) received treatment in the previous 6 months, and (6) show a notable suicidal risk in the diagnostic interview. The trial is open to all German speaking participants residing in Germany, Switzerland, or Austria.

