### Guidance and adherence monitoring

eCoaches support the participants throughout the training by providing content focused guidance and adherence reminders. Guidance can be a beneficial factor of internet interventions (51) and can have a positive effect on treatment adherence (52). eCoaches are psychologists or psychotherapists in training, licensed psychotherapists or trained masters' level psychology students. eCoaches communicate with the participants via the messaging function on the platform. The main role of the eCoach is to motivate, guide participants, and monitor adherence to the treatment as well as risk for deterioration, crisis, or other adverse effects. Within 48 h of module completion, participants receive written feedback on each completed module. Feedback is based on a standardized eCoaching manual which contains preformulated standardized text blocks prepared for each session. The feedback will be individualized for each participant and each module. As adherence is monitored, if participants fail to complete a module within 7 days (14, 21 days) they will receive individualized reminder messages by the eCoach. After 28 days reminders will be sent via text message.

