### Assessments

Clinician-based and self-report assessments will take place at screening (T0), baseline (T1), post-assessment 8 weeks after randomization (T2), 6-month follow-up (T3), and 12-month follow-up in the IC group (T4). There will also be weekly mood assessments during the first seven weeks of the study phase. See Figure 1 for a detailed overview of the study flow and Table 2 for an overview of all assessments. Clinician-based diagnostic assessments will be conducted via telephone.

**Table 2 T2:** Overview of self-report assessments.

**Construct**	**Questionnaire**	**T0**	**T1**	**T2**	**T3**
Demographics	Socio-demographic data (SozDemo)	✓	–	–	–

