**OTHER**					
Moderators of treatment outcome	Risk Factor Questionnaire (RFQ)	–	✓	–	–
Worry	Penn State Worry Questionnaire—Ultra Brief (PSWQ-3)	–	✓	✓	✓
Sleep	One item of Pittsburgh Sleep Quality Index (PSQI)	–	✓	✓	✓
Emotion regulation	Subscales of emotion regulation scale questionnaire (SEK−15)	–	✓	–	–
Incongruence	Incongruence questionnaire—short version (INK-K)	–	✓	✓	✓
Personality	Big Five Inventory (BFI-10)	–	✓	–	–
Behavioral activation	The Behavioral Activation for Depression Scale (BADS-FS−9)	–	✓	✓	✓
Intervention drop-out reasons	Drop-Out Reasons (DG)	–	–	✓	–
Other help	Other help (INH)	–	–	✓	–

T0, screening; T1, baseline; T2, post-assessment; T3, 6-month follow-up.

* *CES-D and GAD-7 assessed weekly until post-assessment*.

Adherence to assessments completion will be monitored throughout the study. In case of noncompliance, study participants will be contacted after 7 (14, 21) days to remind them of assessment completion. After 28 days short messages will be sent via mobile phone.

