#### Primary outcome

The primary outcome will be clinician-based ratings of depressive symptom severity at post-assessment (T2). Clinician-rated depressive symptom severity will be assessed by the QIDS-C (53) which covers nine criteria with 16 items: sleep, sad mood, appetite/weight, concentration/decision making, self view, thoughts of death or suicide, general interest, energy level, and restlessness/agitation. The items are each rated from 0 to 3. A meta-analysis found Cronbach's alpha to be acceptable to good (α = 0.69 − 0.89) (54). Trained psychologists' who are blind to treatment condition will conduct the diagnostic interviews. Interrater reliability will be examined by rating interviews a second time of ~10% of participants by a second rater. Several measures will be taken to ensure blinding: (1) explaining to the participant the importance of keeping the interviewers blinded to randomization status, (2) verbal reminder before each assessment, (3) documentation after each assessment whether the assessor is still blind to study condition.

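### The suicidality rule for the study phase carries over exclusion from the trial; followed literally, it would cost randomised participants their primary outcome

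*Protocol article*

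**What the plan says.** The protocol article deals with suicidality in four places.

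- **Entry.** Under Inclusion and exclusion criteria, the sixth exclusion covers people who "show a notable suicidal risk in the diagnostic interview".
- **The procedure.** Participant safety describes a standardised response to heightened suicidality. Its example is the diagnostic telephone interview, where "individuals will be excluded from study participation and strongly advised to seek help and support", with emergency contact details sent by email.
- **Extension to the study phase.** The same section continues: "This procedure will also be followed should participants show symptoms of suicidality throughout the study phase". It then adds a further step: "participants already included in the study are contacted by an experienced clinician who will determine suicidality symptom severity and discuss next steps".
- **Monitoring.** Under Guidance and adherence monitoring, eCoaches are to "monitor adherence to the treatment as well as risk for deterioration, crisis, or other adverse effects".

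The primary outcome is the clinician-rated QIDS-C at T2, eight weeks after randomisation. Its criteria include "thoughts of death or suicide". Between baseline and T2 both arms complete self-reports: "CES-D and GAD-7 assessed weekly until post-assessment". Clinical analyses specifies intention to treat with multiple imputation, and names demographic and other baseline variables as predictors.

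**The concern.** The extension to the study phase refers back to a procedure in which exclusion is a named element, and no element is exempted. The clinician contact is introduced as an addition, not a replacement. Nothing says that these participants remain in follow-up.

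If staff apply the rule as written, a randomised participant found suicidal before T2 leaves the trial without the primary outcome. The reason for leaving is related to what the QIDS-C measures, and the loss is avoidable. Intention to treat keeps the person in the analysis only through an imputed value, and the named predictors precede the deterioration. The per-protocol analysis, limited to those who completed the primary outcome, would drop the person altogether.

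Detection could also differ by arm. eCoach monitoring for crisis is described only for the training, which the wait-list arm does not receive until six months. The weekly self-reports in both arms soften this contrast, but they are not described as being screened for suicidality. More removals in the intervention arm would flatter the intervention; more in the wait-list arm would do the reverse.

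**Working it through.** **1. Does the text confine exclusion to entry?**

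- The Design section schedules diagnostic interviews at T1, T2 and T3, and Assessments says they are held by telephone. Mention of the telephone interview therefore does not by itself mean before randomisation.
- Assessment of eligibility and randomization places inclusion in the study together with randomisation, after baseline. The already included participants who receive the clinician call are therefore randomised participants.
- No other section limits exclusion to entry or states that these people are still assessed.

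**2. The plan's own figures.** For d = 0.73, 80% power and one-sided alpha 0.05, n per arm = 2 × (1.645 + 0.842)² / 0.73² = 23.2, so 24 per group, as stated. With 100 per arm the detectable effect is (1.645 + 0.842) × √(2/100) = 0.352, matching the stated 0.35.

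**3. Power.** The protocol gives no rate of suicidality after randomisation, so the loss is an assumption. Treating lost outcomes simply as fewer observations:

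| T2 QIDS-C lost per arm | Power for d = 0.35 | Detectable d at 80% power |
|---|---|---|
| 0% | 0.794 | 0.352 |
| 2% | 0.787 | 0.355 |
| 5% | 0.776 | 0.361 |
| 10% | 0.756 | 0.371 |
| 20% | 0.712 | 0.393 |

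Power for d = 0.73 stays above 0.998 throughout. Power is not the issue; bias is.

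**4. Bias.** Define, all as assumptions:

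- k_IC, k_WLC: participants removed before T2 in each arm of 100;
- delta: how much worse, in SD, such a person truly is at T2 than predicted from baseline and arm;
- c: the share of that worsening recovered by imputation. c = 0 if only baseline variables are used; c > 0 if weekly CES-D and GAD-7 scores up to removal are included, which the text does not state.

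Each removed person is imputed delta × (1 − c) SD too favourably, so

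bias in d = delta × (1 − c) × (k_IC − k_WLC) / 100.

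Per excess removal at delta = 1 this is 0.010, 0.0065, 0.005 and 0.003 for c = 0, 0.35, 0.5 and 0.7. Examples at delta = 1:

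| Removed, IC v WLC | c = 0 | c = 0.5 |
|---|---|---|
| 5 v 1 | +0.040 | +0.020 |
| 3 v 1 | +0.020 | +0.010 |
| 3 v 3 | 0.000 | 0.000 |
| 1 v 5 | −0.040 | −0.020 |

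A simulation (3,000 trials per setting, 20 imputations, assumed baseline–outcome correlation 0.5, true d = 0.35) returned the same values with Monte Carlo standard error at most 0.0004. It confirms the formula but says nothing about how often removal would occur.

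**5. Imbalance needed to shift d by 10%.** Imbalance = 0.1 × d × 100 / (delta × (1 − c)). At delta = 1:

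| c | d = 0.35 | d = 0.73 |
|---|---|---|
| 0 | 3.5 | 7.3 |
| 0.35 | 5.4 | 11.2 |
| 0.5 | 7.0 | 14.6 |
| 0.7 | 11.7 | 24.3 |

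For delta from 1.5 down to 0.5, the d = 0.35 figure runs from 2.3 to 7.0 at c = 0, and from 4.7 to 14.0 at c = 0.5.

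**The case against.** The strongest reply is that the authors did not mean this. Exclusion appears only as an example tied to the interview, and it matches the sixth entry exclusion. For people already included, the distinctive step is a clinician's assessment and a discussion of what to do next, which suggests individual judgement and not automatic removal. Current suicidality is listed among the baseline moderators, so some is expected in the randomised sample. A literal rule triggered by any suicidal symptom would be implausibly broad in a depression trial. This makes the benign reading plausible, but it does not settle what staff should do, because the sentence extends the procedure without qualification.

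A second reply is that assessments are never said to stop: analysis is by intention to treat, and assessment completion is monitored with reminders. Those reminders address non-compliance, though, and do not obviously reach someone who has been excluded. Intention to treat with the named predictors does not restore an observed T2 score.

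A third reply is that few people would be affected. No clinician rating is scheduled between baseline and T2, the weekly scales are not described as a suicidality screen, and detection in the T2 interview itself need not cost the outcome. That stands, and it is a main reason for grading the point minor.

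Finally, the article may condense a fuller safety procedure. But this is a rule the article does state, in a form that can be misapplied. A later analysis plan cannot recover interviews that were never held.

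**Conclusion.** The concern holds as a minor one. The safety rule as written reaches randomised participants and includes exclusion; whether the authors intended that is uncertain. If it is followed literally, those detected before T2 lose the primary outcome for a reason related to it.

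The effect on the estimate is probably small: 0.003 to 0.010 in d per excess removal at delta = 1, and about zero if removals are balanced between arms. Its direction is unknown. These figures depend on assumed values for the number removed, their excess severity and the recovery by imputation; the protocol supplies none of them. The point concerns completeness of trial data and not clinical care, since clinician contact is provided for.

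**What to change.** Amend Participant safety to state that:

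- exclusion for suicidality applies only before randomisation;
- randomised participants receive the full safety procedure (advice, emergency contacts, clinician contact) and may stop the training on clinical judgement;
- they continue to be offered the T2, T3 and, in the intervention arm, T4 assessments unless they withdraw consent;
- stopping the training is recorded separately from leaving the study.

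The cost is one or two sentences and a short instruction to interviewers and eCoaches, with no new assessments or staff. The one drawback is that a few participants in crisis will still be invited to assessments, which they may decline. If the authors already intended this, the amendment simply records it.

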### Intervention development and content

The intervention was developed in an expert-driven manner (49). After the initial development phase, the intervention was tested in a small-scale alpha-testing with a group of students. Additionally, four qualitative interviews with students who had completed the intervention were conducted. The collected data was used to make minor improvements and modifications to the intervention content.

The main sessions cover the following topics: behavioral activation: reducing incongruence, behavioral activation: overcoming difficulties and pleasant activity scheduling, psychoeducation on depression and anxiety, cognitive restructuring, problem solving or exposure, and planning for the future. Individual participant tailoring is promoted by providing participants with frequent choices on intervention topics and treatment preferences. In addition to transdiagnostic elements, they can further choose to focus on depression, anxiety, or both disorders, and work through various elective modules on different topics: rumination and worries, acceptance, relaxation, reducing alcohol, self-worth, perfectionism, appreciation and gratefulness, and sleep. See Table 1 for an overview of the sessions and elective modules.

**Table 1 T1:** *ICare Stimmung* training.

**Sessions**	**Elective modules (sessions 2–7)**
1 Behavioral activation: reducing incongruence	
2 Behavioral activation: overcoming difficulties and pleasant activity scheduling	Rumination & worries, acceptance, relaxation, reducing alcohol, self-worth, perfectionism, appreciation and gratefulness, sleep
3 Psychoeducation	
4 Cognitive restructuring	
5 Problem solving I or exposure I	
6 Problem solving II or exposure II	
7 Plan for the future	
8 Booster session	

Elective modules can freely be chosen based on participant preference throughout the intervention. Furthermore, participants can opt to receive tiny tasks which consist of short motivational notifications and small transfer tasks sent throughout each day during the intervention phase through the app. Furthermore, the intervention strongly relies on content tailoring which engages the participant to make real-time choices among various response options by providing immediate content based on participant preference or need. Participants can choose between two versions of the tiny tasks, the light version (three notifications per day), intensive version (five notifications per day), or they can choose not to receive notifications. The tiny tasks are sent through an additional app component which participants can install on their smartphone. They can also use the app for their diary entries.

The intervention content consists of texts, testimonials, audios, short educational video clips, and interactive elements such as quizzes. To foster self-efficacy and stabilize the long-term learning process, participants are instructed from the beginning to integrate and practice newly acquired strategies in their daily life, e.g., through scheduling individualized weekly activity plans, using online diaries, and receiving daily tiny tasks. At the beginning of each session, participants review the previous session content and evaluate how the practicing of homework worked. Sessions are estimated at ~60 min and participants are advised to do one session per week and a maximum of two. Therefore, the training is supposed to last 4–7 weeks. Responsive web-design enables the training to be completed on any kind of internet-ready device. The read-aloud function allows participants to follow the intervention also through narration.

#### Behavioral activation: reducing incongruence (session 1)

Participants are introduced to core functionalities of the training in the first session, such as testimonials, diaries, videos, and the tiny tasks sent through the app. The first session aims at teaching techniques to reduce incongruence between individual perceptions and goals and thereby enhance psychological well-being. This concept is based on the consistency theory by Grawe (50). Participants are encouraged to explore their personal needs and values and work through ways to align their behavior and strengthen the corresponding life areas. Participants are encouraged to formulate individual treatment goals, thereby intending to strengthen motivation. The goals are to be realistic and concrete and can be modified throughout the training. Treatment success, progress difficulties, and individual coping strategies they might face can be documented in the activity diary.

#### Behavioral activation: overcoming difficulties and pleasant activity scheduling (session 2)

The second session provides strategies to overcome difficulties concerning the active implementation of planned activities and offers input on how to reduce avoidant behaviors related to non-implementation of homework. As activities to restore congruence from session 1 might not be self-rewarding in the short-term, the second session also focuses on rather short-term mood-enhancing activities. Participants are encouraged to plan such individually chosen activities for the following week.

#### Psychoeducation (session 3)

Psychoeducational information on depression and anxiety is provided, and factors of etiology and maintenance are explained. To deepen understanding of depression and anxiety, influencing factors, risk factors, and factors of upkeep are presented. There is a short excurse on antidepressants. After a general overview, participants can choose throughout the session whether they would like to receive more detailed information on depression, anxiety, or both. Participants are encouraged to explore their previous and current symptom history, and describe the course of their symptomology.

#### Cognitive restructuring (session 4)

Participants are educated on the causal relationship between cognitions, emotions, and behavior. A thought protocol is introduced which is divided into three components: situations, thoughts, and consequences. Participants can individualize their personal thought protocols by including personal situations, cognitions, and emotions. The second phase of the thought protocol contains questioning the reality basis of negative thoughts, and intends for participants to identify positive and helpful thoughts and to generally concentrate on and practice positive thinking habits.

#### Problem solving or exposure (session 5−6)

At this stage in the training, participants can choose whether they would like to work on either problem solving or practice exposure to fear-inducing situations. In problem solving participants are educated on the distinction between solvable and unsolvable problems and they are supposed to assign their individual problems to these two categories. Following this is the concept of a 6-step problem-solving plan in which they (a) identify an individual problem, (b) define a realistic target state, (c) explore possible solutions and decide on the most promising, (d) set up a detailed solution plan, (e) execute the plan, and (f) verify the implementation process. Participants are encouraged to practice their plan the following week in real life situations. They evaluate the success or failure of the plan in the following session and can then opt to modify their plan accordingly.

Participants focusing on reducing their anxieties learn about avoidant and safety behavior, the concept of habituation through frequent confrontation of fear, and at the end of the session participants should practice what they have learned in theory, and expose themselves to fear-inducing situations. The mechanisms of exposure are explained in detail, highlighting the physical and psychological processes, with an emphasis placed upon the effectiveness of this strategy in the long run for overall well-being compared to avoidant strategies. Participants are requested to identify individual difficult or fear-inducing situations in an anxiety hierarchy. They are advised to start with their least fearful situations and to increase intensity by enhancing practice. In a challenge management protocol, participants can practice exposure in a theoretical mindset. In the next session, they evaluate the success of the implementation of their plan. They can also identify personal safety behavior and are prepared to focus on a more challenging situation which they are supposed to practice the following weeks.

#### Plan for the future (session 7)

Participants see brief content summaries in the 7th session and are asked to review the progress they have made concerning individual training goals. Participants are instructed to identify training mechanisms and strategies which helped them in reducing symptoms of depression and anxiety. They are able to write a personal letter addressed to themselves in which they assume they have completed four more weeks of practicing newly acquired strategies and can set goals for the coming 4 weeks.

#### Booster session (session 8)

In the booster session, which participants receive 4 weeks after completion of the 7th session, participants can reflect on their learning experience and individual goal attainment. They are encouraged to explore their current state of mental health and receive additional resources on support if needed. They are also able to review the letter to themselves, can reassess their goals and are instructed to make plans to implement their intentions and actions in the following months.

